### Randomization

2.5

The random sequence will be generated by PROCPLAN in the SAS software and the entire process is operated by the teacher of the Statistics Department of Chengdu University of Traditional Chinese Medicine. The results of the random sequence will be hidden and spread using opaque envelopes.

### Blinding

2.6

The study was a double-blind clinical trial. All researchers, subjects, and statisticians were blinded throughout the intervention period. Unless participants have serious adverse events to receive emergency treatment, they cannot eliminate blindness. Both the FBD and the placebo granules will be produced by the Pharmacy Department of Hospital of Chengdu University of Traditional Chinese Medicine. Both are ensured to be consistent in appearance, shape, or odor and specifications. Moreover, ordinary dressings must also be no different from silver ion dressings in terms of appearance and smell. It is worth mentioning that research members cannot discuss with the participants their possible treatment options.

### Diagnostic criteria

2.7

#### Western medicine diagnostic criteria

2.7.1

Participants not only need to comply with the diagnostic criteria for diabetes WHO diagnostic criteria in 1999^[26]^ (Table 1), but also follow the diagnostic and grading criteria for DF produced by The International Working Group on the Diabetic Foot (IWGDF)^[27]^ (Table 2).

**Table 1 T1:**
[figure not shown]
WHO diagnostic criteria for diabetes.

**Table 2 T2:**
[figure not shown]
IWGDF diagnostic and grading criteria for diabetic foot.

#### TCM diagnostic criteria

2.7.2

Referring to classification criteria for gangrene in the “Guiding principles for new drug clinical research of TCM,”^[28]^ the detailed diagnostic items are shown in Table 3.

**Table 3 T3:**
[figure not shown]
Classification criteria of gangrene for traditional Chinese medicine.

### Eligibility criteria

2.8

Inclusion criteria:

1.Diagnosis of DF according to WM and TCM.2.According to Wagner classification of DF, patients with stages II, III, IV are eligible.3.Aged between 18 and 75 years old.4.Voluntarily participate in the test and sign the informed consent.

Exclusion criteria:

1.Patients with cardiac and renal insufficiency, acute coronary syndrome, cerebrovascular accident, hematopoietic system disorders and mental diseases, malignant tumors and end-stage patients.2.Women who are breastfeeding, pregnant, or preparing for pregnancy.3.Allergies for known drugs or experimental drugs.4.Uncooperative during the experiment.5.Having a history of alcoholism or drug abuse.6.Having a history of another clinical study in the previous 1 month.

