### Design

2.1

This study is a multicenter, double-blind, randomized, placebo controlled clinical trial, and the protocol was registered in Chinese Clinical Trial Registry on July 16, 2019, ChiCTR1900024557. Sixty eligible participants signed the informed consent and were randomly assigned to the experimental or control group at a ratio of 1:2. Both groups received the same basic treatment for DF disease, the experimental group was additionally washed with FBD and ordinary dressing changes, while half of the patients in the control group received placebo and ordinary dressings, and the other half received placebo and silver ion dressings. The purpose of this trial is to explain the efficacy and safety of herbal medicine FBD for DFI compared with western medicine (WM) alone. This study will adhere to the standard protocol items: Recommendations for Interventional Trials (SPIRIT) 2013 statement, and flow chart of the study will be used to show the screening process (Fig. 1).

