### Sample size

2.4

This study is a superiority clinical trial with interleukin 6 (IL-6) as the main efficacy indicator, so we chose the mean superiority test of 2 independent samples to estimate the sample size. According to the previous relevant references,^[25]^ the optimal response rate was set to 0.04. The mean values of the experimental group and the control group were 6.14 and 6.21, and the combined standard deviation of the 2 groups was 0.14. At the same time, set *a* to 0.025 and *b* to 0.2. Enter the above values into the Power Analysis and Sample Size version 11.0 (PASS 11.0) software to calculate the sample size for the experimental group as 20 and the control group as 40. Finally, the total number of study samples is determined to be 60 cases.

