### Statistical analysis

3.5

The data of the study will be analyzed by statistical analysis software packages SPSS 23.0 and will be performed by experts from the Statistics Teaching and Research Office of Chengdu University of Traditional Chinese Medicine. The measurement results was calculated by *t* test, and the results were expressed as “mean ± standard deviation.” Chi-squared test was used to analyze the count data. The paired design *t* test was used for comparison the differences between before and after treatment with the same group, and the independent sample *t* test was used for comparison the differences between groups. The comparison of incidence of adverse events between the 2 groups using Chi-squared test or Fisher exact probability method. If *P* < .05, it was considered as a statistically significant difference.

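### Wagner grade is known for every patient at entry, but the stated between-group t test cannot use it; an ANCOVA adjusted for grade and baseline would recover precision at almost no cost

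*Protocol article*

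**What the plan says.** Protocol article, section 2.8 (Eligibility criteria), inclusion criterion 2: "According to Wagner classification of DF, patients with stages II, III, IV are eligible". The criterion cannot be applied without grading the foot, so grade is on record before allocation.

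Section 2.1 (Design): patients are "randomly assigned to the experimental or control group at a ratio of 1:2". Within the control group, "half of the patients in the control group received placebo and ordinary dressings, and the other half received placebo and silver ion dressings".

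Section 2.4 (Sample size): "This study is a superiority clinical trial with interleukin 6 (IL-6) as the main efficacy indicator". The calculation leads the authors to "calculate the sample size for the experimental group as 20 and the control group as 40". Its inputs are means of 6.14 and 6.21, a common SD of 0.14, a value of 0.04, alpha 0.025 and beta 0.2.

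Section 2.5 (Randomization): "The random sequence will be generated by PROCPLAN in the SAS software". The section also names the operator and opaque envelopes. It mentions neither blocks nor strata.

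Section 3.2 (Outcome measures): IL-6 and TNF-α are measured before treatment and weekly during it.

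Section 3.5 (Statistical analysis): an independent-samples t "test was used for comparison the differences between groups", and a paired t "test was used for comparison the differences between before and after treatment with the same group". No covariate is named.

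**The concern.** Patients from Wagner II to Wagner IV are pooled in a trial of 60. It is plausible, though the article gives no figure for it, that severity at entry is related to wound area, walking, IL-6 and TNF-α. If so, two things follow from analysing with a t test.

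First, the variation between grades is counted as noise in every comparison, even when the groups happen to be balanced. Second, if one group draws more severe feet by chance, the estimated differences for several outcomes may move together, and the stated analysis has no means of correcting for it. At stake are the width of the confidence intervals and how far a reader will trust the one realised comparison. The validity of the test is not at stake.

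**Working it through.** **1. The plan's own figure.** Inputs are from section 2.4. With 1:2 allocation, the experimental group needs n = (1.960 + 0.842)² × SD² × 1.5 / d², and the control group 2n. With SD 0.14:

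- d = 0.07 (6.21 − 6.14): n = 47.1, so 48 v 95 (48 v 96 by the t calculation).
- d = 0.07 − 0.04 = 0.03: n = 256.4, so 257 v 513.
- d = 0.07 + 0.04 = 0.11: n = 19.1, so 20 v 39 (20 v 40 by the t calculation).

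Of these three differences, only 0.11 at one-sided 0.025 gives the stated 20 v 40. That is a separate question about the sizing. It matters here only because power has to be shown for both 0.07 and 0.11.

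**2. Chance imbalance in grade.** The article gives no grade mix, so let a severity stratum hold a share p of patients (assumed). Under simple randomisation the SD of the difference in shares is √[p(1 − p)(1/20 + 1/40)]. The probability of a difference of at least 20 points is an exact sum over two independent binomials.

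| p (assumed) | SD of difference, 20 v 40 | P(≥ 20 points), 20 v 40 | P(≥ 20 points), 20 v 20 |
|---|---|---|---|
| 0.20 | 0.110 | 8.6% | 16.4% |
| 0.30 | 0.125 | 13.5% | 22.6% |
| 0.50 | 0.137 | 17.1% | 26.8% |

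The 20 v 40 column is the planned comparison. The 20 v 20 column would apply only to a contrast of the foot-bath group with one dressing half of the control group, which section 3.5 does not state.

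**3. What an imbalance could do to one estimate.** Suppose a stratum's mean IL-6 differs from the rest by 0.5 to 1 SD (assumed). A 20-point imbalance then moves the observed difference by 0.20 × 0.5 × 0.14 = 0.014 to 0.20 × 1 × 0.14 = 0.028. That is 20% to 40% of the planned 0.07.

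**4. Gain from adjusting.** Let R² be the share of outcome variance explained by grade (assumed; not in the article). The residual SD is 0.14 × √(1 − R²), and the equivalent unadjusted total is 60/(1 − R²). Power is from the noncentral t at 20 v 40, one-sided 0.025, with standard error = residual SD × √(1/20 + 1/40).

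| R² | Residual SD | Equivalent N | Gain | Power, d = 0.07 | Power, d = 0.11 |
|---|---|---|---|---|---|
| 0 | 0.140 | 60 | 0% | 0.43 | 0.81 |
| 0.05 | 0.136 | 63 | 5% | 0.45 | 0.82 |
| 0.10 | 0.133 | 67 | 11% | 0.47 | 0.84 |
| 0.20 | 0.125 | 75 | 25% | 0.52 | 0.88 |
| 0.30 | 0.117 | 86 | 43% | 0.57 | 0.92 |

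Giving up one or two of the 58 degrees of freedom changes these powers by less than 0.001.

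**The case against.** **The t test is valid.** An unadjusted comparison of randomised groups has the right error rate, and that rate already allows for chance imbalance. This stands. A reader might infer that a severity imbalance biases the trial or inflates type I error; the stated design and analysis give no ground for that. The loss is of efficiency and credibility.

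**The randomisation may already be stratified.** A reader might infer that grade is ignored in allocation as well. Section 2.5 does not say so: it is silent on strata and blocks, and a condensed article often omits them. Two strata in each of three hospitals would also mean six lists averaging 10 patients, which is a debatable trade. The point therefore makes no claim about allocation. If grade were in fact balanced by the list, the imbalance figures in step 2 would fall away, but the stated t test would still leave between-grade variation in its error term.

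**Covariates are SAP matter.** Silence about covariates would be no finding. Here, though, section 3.5 positively names the test, and that test cannot carry a covariate.

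**The arms are not 20 v 20.** Correct: the sized comparison is 20 v 40, so the larger imbalance figures do not describe the planned analysis.

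**The size is assumed, and baseline may do the work.** Also fair. The article gives neither a grade mix nor a relation between grade and any outcome. Section 3.5 does not say whether the t test uses final values or changes; a change score in IL-6 would already remove part of any difference due to grade. What counts is what grade adds beyond baseline, and that may be small. A two-level split also cannot explain more than the three grades do. None of this favours the t test over a model that includes both terms.

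**Conclusion.** The point holds for the analysis. Grade is known at entry, and the stated between-group test has no way to use it. In the planned 20 v 40 comparison, a 20-point or larger imbalance in a stratum holding 20% to 50% of patients has a chance of about 9% to 17%, assuming simple randomisation. Adjustment is worth about 5% to 43% more patients if grade explains 5% to 30% of outcome variance, and nothing if it explains none.

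It is an inexpensive improvement in precision, not the correction of an error. Nor does it rescue the sample size: at a difference of 0.07, adjustment alone would need an R² of about 0.58 to reach 80% power. The precision figures apply to the continuous outcomes only and do not carry over to wound pathogen distribution.

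**What to change.** In section 3.5, for IL-6, TNF-α, wound area and the walking outcomes, replace the between-group t test with an ANCOVA fixed before unblinding. Include treatment group, Wagner stratum (II v III-IV) and, for IL-6 and TNF-α, the pre-treatment value that section 3.2 already collects. Report the adjusted difference with its confidence interval; the unadjusted t test can be kept as a supporting analysis.

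The cost is about one degree of freedom for the stratum and one for the baseline value where used, out of 58. No new data are needed, and eligibility, treatment and the randomisation list stay as they are.

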### Termination and withdrawal criteria

2.9

All participants were informed that they had the right to drop out of the study before starting the experiment. The test will also be withdrawn or terminated if the following criteria occur.

1.Side effects and adverse reactions occur, which are difficult for patients to tolerate.2.Serious adverse events occurred.3.Complicated with other diseases during the test.4.Patients with poor compliance and failed to perform research protocol as required.

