### Treatment plan

3.1

Both groups received based on dietary treatments recommended by the Diabetes UK evidence-based nutrition guidelines for the prevention and management of diabetes,^[29]^ and controlled blood glucose, lowered blood lipids, adjusted blood pressure, and suppressed infections according to individual conditions during the trial period. At the same time, DF ulcers can be treated by surgical debridement to remove necrotic tissue, improve lower limb circulation and a routine dressing every 2 to 3 days according to the Diabetic Foot Ulcer Treatment Guidelines.^[30]^

Experimental group: The participants in experimental group took a foot bath 1 to 2 times a day. Each bag of FBD was dissolved in 300 mL of warm water for 30 minutes, then cover the wound with a ordinary dressing.

Control group: The patients in the control group will be given a placebo decoction for foot bath twice daily for 30 minutes. The immersion method is the same as the experimental group. In contrast, half of the patients covered the wound with an ordinary dressing and half with a silver ion dressing.

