### Outcome measures

3.2

Primary efficacy outcomes:

1.IL-6 and tumor necrosis factor α (TNF-α) were detected by enzyme-linked immunosorbent assay and were measured before and each week after treatment during entire treatment.2.Wound pathogen distribution: Collect samples of ulcers and use a fully automatic microbiologic tester for bacterial detection once a week.

Secondary efficacy outcomes:

1.Blood glucose and blood lipid: The blood glucose, total cholesterol, triglyceride, low-density lipoprotein cholesterol, and high-density lipoprotein cholesterol are detected by a fully automatic biochemical analyzer.2.Wound area: Long multiplied by high area. First take a picture of the wound and then read the data with Image J software. The above operations are performed by the same doctor.3.Lower extremity blood vessel diameter, blood flow velocity: detected by lower extremity blood vessel Doppler ultrasound.4.Walking speed, walking distance: Make patients walk on a flat ground with a scale, and calculate the distance and speed.5.TCM syndrome score: Recorded with TCM Syndrome Score Evaluation Form.

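### Exclusion criterion 4 and the section 2.9 withdrawal rules act on behaviour after randomisation and can end outcome collection, which opens the comparison to selection bias of unknown size and direction

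*Protocol article*

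**What the plan says.** Protocol article, section 2.8: exclusion criterion 4 is "Uncooperative during the experiment". The other five exclusion criteria are conditions that can be checked at screening.

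Section 2.9 introduces its list with "The test will also be withdrawn or terminated if the following criteria occur". The list covers intolerable side effects, serious adverse events, another illness arising during the trial, and "Patients with poor compliance and failed to perform research protocol as required". It does not say whether a patient who meets one of these stops the bath only or leaves the study altogether.

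Section 2.1 says that eligible patients consented and were "randomly assigned to the experimental or control group at a ratio of 1:2". Section 3.2 has IL-6 and TNF-α "measured before and each week after treatment during entire treatment", with wound cultures once a week. In section 3.5 an independent-sample t "test was used for comparison the differences between groups".

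**The concern.** Eligibility has to be settled before allocation. A criterion that can be met only during the trial lets a randomised patient become ineligible in retrospect. The same conduct is also a withdrawal reason in section 2.9, and a patient labelled ineligible is more easily left out of an analysis than one labelled withdrawn.

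Cooperation with daily soaking of an ulcerated foot can depend on how well the bath is tolerated and how the wound is doing, so it lies downstream of treatment. The same is true of intolerable reactions, serious adverse events and some intercurrent illness. If meeting a section 2.9 criterion ends participation, the weekly primary measurements end with it, and no later analysis can recover values that were never collected. The patients who remain may then differ between arms for reasons other than the effect of the bath. With 20 patients planned in the experimental arm, two to four removals are 10–20% of it.

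**Working it through.** **Setting the sections side by side.** Section 2.1 places eligibility before allocation, while criterion 4 in section 2.8 refers to conduct during the trial. Both cannot hold literally. Section 2.9 item 4 already covers in-trial non-compliance, so criterion 4 either duplicates it under an eligibility label or was meant as a screening judgement. On timing, section 3.2 ties the primary measurements to the treatment period, so ending participation would be expected to end them.

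**Inputs from section 2.4.** Planned means are 6.14 and 6.21, a difference of 6.21 − 6.14 = 0.07. The SD is 0.14, the arms are 20 and 40, and α is 0.025 (taken here as one-sided; the article does not say). The stated 20/40 is reproduced with a t-based calculation at 80.5% power only if the 0.04 margin is added to the difference (0.07 + 0.04 = 0.11). That is a separate matter and does not affect this point.

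**Not in the documents.** The number removed, the arm they come from and how their IL-6 differs are not given. All three are assumed below.

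**Illustration 1: fixed gap.** Shift in an arm's mean = proportion removed × (mean of removed − mean of retained).
- 3 of 20 experimental patients removed, IL-6 one SD above the rest: 3/20 × 0.14 = 0.021, and 0.021/0.07 = 30% of the planned difference, in favour of the experimental arm.
- The same proportion and gap in control as well (6 of 40): 6/40 × 0.14 = 0.021. The net shift in the difference is 0.021 − 0.021 = 0.
- The same loss in control only: 0.021 the other way, in favour of control.

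**Illustration 2: selection model.** Assume no true effect and removal only from the experimental arm. A fraction r with the strongest tendency to leave is removed, and that tendency is normal and correlated ρ with high IL-6. The retained mean falls by b = ρ × φ(z₁₋ᵣ)/(1 − r) in SD units, with standard error √[1/(20(1 − r)) + 1/40]. One-sided type I error = 1 − Φ(1.96 − b/SE).

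For r = 10%, φ(z)/(1 − r) = 0.195 and SE = √(1/18 + 1/40) = 0.284. For r = 20%, they are 0.350 and √(1/16 + 1/40) = 0.296.

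| Removed (of 20) | ρ | Bias in IL-6 (b × 0.14) | Share of 0.07 | Type I error |
|---|---|---|---|---|
| 2 (10%) | 0 | 0 | 0% | 2.5% |
| 2 (10%) | 0.3 | 0.008 | 12% | 4.0% |
| 2 (10%) | 0.5 | 0.014 | 19% | 5.3% |
| 4 (20%) | 0 | 0 | 0% | 2.5% |
| 4 (20%) | 0.3 | 0.015 | 21% | 5.4% |
| 4 (20%) | 0.5 | 0.025 | 35% | 8.6% |

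**If removal is unrelated to outcome**, only power is lost. Equal removal of 5, 10 or 20% leaves 19/38, 18/36 or 16/32. Power at the effective distance of 0.11 falls from 80.5% to 78.4, 76.2 or 71.0%.

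**The case against.** The strongest reply is that criterion 4 is loose wording. Section 2.1 randomises patients already found eligible, the other exclusions are screening conditions, and section 2.9 has its own compliance rule, so the authors may have meant patients expected to be uncooperative. That is plausible. It does not rescue the text, which says otherwise, and it supports the same one-line repair.

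A second reply is that section 2.9 does not say data are dropped or visits cease, and that analysis sets and handling of withdrawn patients are commonly left to an analysis plan, which is not shown here. This stands in part. The silence on analysis sets is not a fault. What remains is a stated rule that ends participation on post-randomisation grounds, and an analysis plan cannot supply measurements that were not taken.

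Three stronger readings are tempting, and the documents do not support them:
- *The rules break the randomised comparison.* If every randomised patient were still followed and analysed as allocated, it would be protected. The rules open it to bias, and the document does not show that bias occurs.
- *The bias favours the experimental arm.* Section 3.1 has "The participants in experimental group took a foot bath 1 to 2 times a day", while control receives a "placebo decoction for foot bath twice daily for 30 minutes". Stated bath frequency is equal or heavier in control, so loss driven by burden could fall more on that arm and favour control. The two schedules need reconciling in any case. The matched placebo and blinding also limit arm-dependent judgements of cooperation, though not differences in tolerability.
- *Adverse outcomes are undercounted.* A reaction that triggers withdrawal has been observed. Section 3.4 calls for detailed records and written reports of drug-related events, and section 3.5 compares incidence between arms. At most, events after withdrawal could be missed, and the article does not say that they would be.

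**Conclusion.** The point holds as a defect in two stated rules. Criterion 4 is not a baseline condition as worded. Section 2.9 does not separate stopping the bath from leaving the study, so applying it literally can remove randomised patients for treatment-related reasons and end their primary-outcome collection. The consequence is exposure to selection bias, with size and direction unknown.

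The 12–35% of the planned difference and the type I error of about 4.0–8.6% show only what is possible. They require removal of 10–20% from the experimental arm alone and a correlation of 0.3–0.5 with IL-6, none of which comes from the documents. The 30% figure likewise needs one-sided removal and a full-SD gap. Confidence is high on the wording and low on any particular amount of bias. The change is worth making because it is cheap before data collection and cannot be made good afterwards.

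**What to change.** - **Section 2.8:** delete exclusion criterion 4, or restate it as a judgement made and recorded at screening, before randomisation.
- **Section 2.9:** distinguish stopping the study bath from leaving the study. Patients who stop or comply poorly stay in the scheduled IL-6, TNF-α, culture and safety assessments unless they withdraw consent. The clinical reasons for stopping treatment stay as they are.
- **Section 3.5:** state that these patients are analysed in the group to which they were allocated, with any compliance-based exclusion confined to a secondary analysis. If an analysis plan already says so, a cross-reference is enough.

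The cost is protocol wording, a few more follow-up visits, and some dilution of the estimated effect from patients who did not comply. The planned total of 60 does not change.
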